#### Interventions

There will be four treatment arms to the study; leaflet and advice; joint protection delivered by an occupational therapist in a group setting; hand exercises delivered by an occupational therapist in a group setting; and joint protection combined with hand exercises delivered by an occupational therapist in a group setting.

Previous studies suggest that people with hand OA do not consult their GP very often about their symptoms and adopt their own approaches to self-management, which may or may not have beneficial effects. In order to standardise information given to participants, all eligible participants will receive information on GP headed notepaper from a research nurse prior to randomisation. Participants will be instructed to continue with their own self-management approaches, which they will be asked to record, will receive standardised advice on the use of analgesia and will be given the Arthritis Research UK leaflets 'Osteoarthritis' and 'Looking after your joints when you have arthritis' http://www.arthritisresearchuk.org. Relevant sections in the booklets will be highlighted and discussed. A leaflet on GP headed notepaper, which includes general information on looking after the joints of the hand, how to use the leaflets, and advice to consult their GP if symptoms continue to be troublesome, will be provided. Participants will also receive NICE good practice guidance [37] and advice on effective pain management with the use of paracetamol as first line analgesia, and advice on when to consult their GP. Co-interventions will be recorded and avoided during the first six months of the study.

##### Leaflet and advice

The intervention will be delivered as described above without any additional OT classes.

##### OT Interventions

Participants randomised to any one of the OT interventions will receive in addition to the above, four group sessions held once a week with 4-6 participants. A pool of 12 OTs will be trained to deliver the interventions. In order to develop rapport between participants and therapist it is planned that the same OT will conduct all four sessions. Non-trial co-interventions e.g. splinting, will be avoided during the first six months of the study and recorded if given. To reduce any potential bias, each OT will rotate throughout the interventions every three months. Rotation will be determined by the availability of the OTs to deliver the specific intervention, that is, the single component interventions, or the combined programme.

All three OT interventions will include a general introduction, education on hand OA and its management, and management of pain during everyday activities. The OT interventions will be supported by leader and participant manuals which will be used to promote treatment adherence and to standardise delivery of the OT interventions. Flipcharts will be used as teaching aids, which will identify key points to be addressed within each session, and copies of the pre-written charts will be included in the leader manuals.

Participants will be encouraged to practice techniques taught in the sessions and illustrated in the participant manual, by setting weekly action plans, homework programmes and weekly review of progress. Participants will be encouraged to continue with their own self-management approaches, which they will be asked to record in their participant manual.

###### *Joint protection classes*

The OT intervention will be based on that previously used in inflammatory arthritis and adapted for hand OA, with particular attention to hand and thumb problems [11,12]. Supervised kitchen activities will be undertaken with participants in pairs to allow demonstration and practice of new skills. Classes will be delivered over 4 group sessions (maximum 1 hour each session).

###### *Hand exercise classes*

Hand exercises to strengthen muscles and mobilise joints will be developed from those identified in the consensus workshops. These will form the basis of the exercise classes which will be demonstrated and practised with participants seated around a large table. Classes will be delivered over 4 group sessions (maximum 1 hour each session).

###### *Joint protection with hand exercises*

Participants will receive both joint protection and hand exercises over 4 group sessions (maximum 11/2 hours each session).

### Audit of OT interventions

In addition to the standard proforma, an audit for the group intervention will be devised based on the leader manuals. The study co-ordinator will use these to carry out random audits to assess adherence to the intervention protocol.

### Monitoring and reporting of harms

If a patient experiences an adverse event the OT concerned will inform the study coordinator by fax or telephone. The co-ordinator will investigate and record all details of the incident on an "adverse event" form. The Principal Investigator will be notified of the event, and will determine any follow-up action as required, e.g. referral to the participant's GP. All adverse events will be reported to the Data Monitoring Committee and the Trial Steering Committee.

### Equipment

All OT sites will be provided with a standardised equipment package for the delivery of the joint protection and exercise programmes. An equipment inventory is available on request from the study co-ordinator.

### Electronic OT mailing list

In order to enhance protocol adherence and to offer support to the OTs involved in the trial, the Principal Investigator and study co-ordinator will set up a shared electronic mailing list for participating therapists.

### Pilot study

Up to 6 participants will be invited to attend a pilot study of the OT intervention. These participants will be members of the Centre Research Users Forum and will have a history of hand OA. The pilot study will be based on the combined programme of hand exercises and joint protection, and will take place at a local OT Department. The study will test processes and procedures, and any further amendments to the content of the intervention will be made prior to the commencement of the main trial.

Social class [65]	Higher managerial/Higher professional/Lower managerial or professional/Intermediate occupations/Self employed/Lower supervisory or technical/Semi-routine/Routine	HS, 0NA
Age when left school	Years	HS
Leave school to go to full-time education or university	Yes/No	HS
Age when finished full time education	Years	HS
Gained qualifications through study as an adult	Yes/No	HS
Ethnic origin	White UK or European/AfroCaribbean/Chinese/Asian /African/Other	HS
Height	Feet and inches or centimetres	HS
Weight	Stones and lbs or kilograms	HS

*Measures to define trial inclusion/exclusion *		

Hand pain in the last year	Yes/No	HS
Pain, aching or stiffness in your hands in the last month [30]	No days/Few days/Some days/Most days/All days	HS, 0Q, 0NA, 3, 6NA, 12
Seen OT or PT for hand problem in last 6-months	No/Right hand only/Left hand only/Both hands	HS, 0NA^1^
Injured hands badly enough to see a doctor in last 6 months	No/Right hand only/Left hand only/Both hands	HS, 0NA^1^, 6NA
Had a hand operation in the last 6 months	No/Right hand only/Left hand only/Both hands	HS, 0NA^1^, 6NA
Joint injection (fingers, thumbs or wrist) in the last 6 months	No/Right hand only/Left hand only/Both hands	HS, 0NA^1^
Clinical red flags (e.g. swollen painful hot hands or recent trauma to the hands)	Yes/No	0NA, 6NA
Clinical assessment for hand swelling, nodes, enlargement or deformity	Yes/No for joints required to apply the ACR criteria for hand OA (ref)	0NA

*Characteristics of hand problem*		

Handedness	Right/Left/Both	HS, 0NA, 6NA
Hand problems in the last year	Yes/No	HS
Hand pain location in the last year	Right/Left/Both	HS, 0NA^2^, 6NA^2^
Hand pain manikin [43]	Hand area shaded to represent pain	0Q, 3, 6Q, 12
Hand that gives most problem	Right/Left/No difference	HS, 0NA, 6NA
Number of days with hand pain in the last year [66]	Less than 7 days/1 to 4 weeks/> 1 month and < 3 months/3-months or more	HS
Hand pain severity in the last month	NRS: 0-10 (no pain to pain as bad as could be)	0Q
Bothersomeness of hand problems (adapted from [67])	Not at all/slightly/moderately/very much/Extremely	0Q, 3, 6Q, 12
Thumb pain during activity in the last month	Yes/No	0NA, 3, 6NA, 12
Ability to make a fist [68]	Right: yes/no/unable; Left: yes/no/unable	0NA, 6NA
Length of time with a hand problem	HS-years 0NA-Separate response for right and left hand < 12 months/1 to 5 yrs/5 to 10 yrs/10+ yrs	HS, 0NA
Previous hand surgery	Operation details, which hand, timing (< 1 yr ago/1 to 5yrs ago/5 to 10yrs ago/10+ yrs ago)	0NA, 6NA^3^
Previous hand injury	Injury details, which hand, timing (< 1 yr ago/1 to 5yrs ago/5 to 10yrs ago/10+ yrs ago)	0NA, 6NA^3^
Past or present job involved excessive use of hands	Yes/No	HS
Past or present hobbies or pastimes involved excessive use of hands	Yes/No	HS
Global assessment of change in hand pain since baseline [41]	Completely recovered/much better/better/no change/worse/much worse	3, 6Q, 12
Global assessment of change in ability to use hands since baseline [41]	Completely recovered/much better/better/no change/worse/much worse	3, 6Q, 12

*Body pain and shoulder function*		

Pain elsewhere (body manikin)	Body area shaded to represent pain lasting for a day or longer in the last 4 weeks	HS, 3, 6Q, 12
Ability to put hands behind head [68]	Right: yes/no/unable; Left: yes/no/unable	0NA, 6NA

*Perception, impact and quality of life*		

Illness perceptions	Subset of questions from the illness perceptions questionnaire revised (IPQ-R) [45,51]	HS, 0Q, 3, 6Q, 12
Participation restriction (selected questions from [46])	All the time/most of the time/some of the time/A little of the	0Q, 3, 6Q, 12
- Self-care needs met as and when wanted	time/None of the time	
- Home looked after as and when wanted		
- Belongings looked after as and when wanted		
Hand problems make you feel frustrated in the last month [45]	All days/most days/some days/few days/no days	0Q, 3, 6Q, 12
Adaptation behaviours		0NA, 6NA
- Use gadgets	Yes/No to each question	
- Help from another person		
- Avoidance		
- Find a different way of doing something		
- Stopping/reducing activities		
- Things take longer		
- Other (please state)		
Quality of life: EuroQol-EQ5-D [47,48]	(-0.59-1)	0Q, 3, 6Q, 12

Intervention evaluation		

Satisfaction with care received for hand problem	Very satisfied/Quite satisfied/no opinion/not very satisfied/not at all satisfied	3, 6Q, 12
Treatment sessions: Number of appointments	Too many/About right/Not enough/I did not attend any appointments	3
Treatment sessions: Length of each visit	Too long/About right/Too short/I did not attend any appointments	3
Hand exercise frequency [69]	Never/Once a week/Twice a week/Three times a week/Four times a week/Five times a week/Six times a week/Once every day/Twice every day	6Q, 12
Hand exercise frequency in last week [52]	Never/Almost never/Sometimes/Fairly often/Very often/Always	0Q, 3, 6Q, 12
Hand exercise duration [69]	< Five minutes/5-10 minutes/10-15 minutes/15-30 minutes/30 minutes+/I don't do hand exercises	6Q, 12
Behaviour change in last week: energy conservation/fatigue [52]	(1-6) i.e. average of 5 items each rated as: Never/Almost never/Sometimes/Fairly often/Very often/Always	0Q, 3, 6Q, 12
- Regular breaks		
- Breaking up tasks		
- Pacing of activities - Swapping between light and heavy tasks		
- Maintaining good posture whilst sitting, standing, lifting objects or moving about		
Behaviour change in last week: joint protection use [52]	(1-6) i.e. average of 5 items each rated as: Never/Almost	0Q, 3, 6Q, 12
- Use two hands to carry things	never/Sometimes/Fairly often/Very often/Always	
- Avoid gripping or pinching things tightly		
- Change the way everyday activities are completed		
- Use gadgets/labour-saving devices		
- Use stronger, larger joints		
Behaviour change in last week: carry on working through the pain when doing everyday activities [52]	Never/Almost never/Sometimes/Fairly often/Very often/Always	0Q, 3, 6Q, 12

*Health care use and co-interventions*		

Self-report	Self-help remedies, contact with NHS and private healthcare, over the counter medicines, use of hand splints	HS, 0NA, 6Q, 6NA, 12
GP consultation download	Number of follow-up visits to the GP, prescription of medication including NSAIDs and referral for other treatment such as surgery	Continually collected data

*Nurse audit questions *		

Did the participant un-blind you during the assessment?	Yes/No	6NA
If yes, what did the participant say and could it have been avoided?	Text	6NA
If yes, what treatment arm do you think the patient is randomised to	Leaflet and advice/Had OT, but not sure which OT intervention/Had OT, joint protection/Had OT, hand exercises/Had OT, joint protection and hand exercises	6NA

NRS = Numerical rating scale; OT = occupational therapist; PT = Physiotherapist; HS = Baseline Health Survey; 0Q = Baseline Questionnaire; 0NA = Baseline nurse assessment; 3 = 3-month questionnaire; 6Q = 6-month questionnaire; 6NA = 6-month nurse assessment; 12 = 12-month questionnaire; + = included in minimum data collection; 1 = time frame last month; 2 = refers to current hand problem; 3 = time frame last 6 months.

Minimum data collection at each follow-up data collection stage will attempt to capture the primary outcomes, AUSCAN and global change scores, in the event of non-response to the mailed follow-up questionnaire.

#### Secondary and tertiary outcome measures

##### Self-reported questionnaire at baseline, 3, 6 and 12 months

Individual subscales of the AUSCAN (pain, stiffness and function), hand pain manikin [43], average pain severity over the past 3 days (0-10 numerical rating scale), severity rating of participant nominated main functional problem over the past 3 days (0-10 numerical rating scale) [44], satisfaction with hand function over the past 3 days (0-10 numerical rating scale), side effects of treatment and adverse events, co-interventions (from the medical record download: follow-up visits to the GP, prescription of medication including NSAIDs and referral for other treatment such as surgery and from self-reported questionnaires: self-help remedies, contacts with private healthcare, over the counter medicines, use of hand splints), frustration related to hand disability [45], pain elsewhere (pain manikin), participation restriction [46], health-related quality of life using the EuroQol EQ-5D [47,48] and SF12v2 [49], satisfaction with care (3 and 6 months), Arthritis Self Efficacy pain subscale [50], Illness Perceptions Questionnaire-Revised (IPQR) modified for hand OA [45,51] and self-reported behaviour change using selected questions [52].

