### Trial Procedures

#### Recruitment and retention strategies

Standard research centre procedures will be followed to maximise follow up. Non-responders to the health survey will receive a postcard reminder at 2 weeks followed by a second questionnaire 2 weeks later. If there is still no response, no further contact will be made. At 3- and 12-month follow-up, randomised participants will receive postcard reminders and follow-up questionnaires. Non-responders will be approached for Minimum Data Collection (MDC) 2-weeks after the second questionnaire is mailed. MDC is a shorter version of the health survey questionnaire and will be used to collect the primary outcome measure (OARSI/OMERACT responder criteria) along with date of birth, age and gender to ensure the data are provided by the intended participant. MDC is completed on the telephone, or by post where consent to telephone contact has not been given. The reminder process for baseline and 6 month nurse clinic attendance will include an initial invitation to attend the clinic, and a reminder sent two weeks later. At 6-months, if there is still no response, the follow-up questionnaire will be mailed to participants but without an invitation to attend the clinical assessment. If there is still no response after a further 2 weeks, MDC will be completed if possible. Participants failing to attend an assessment appointment will be offered a second appointment. At all stages of the trial, any reason for non-participation will be recorded, if given.

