A sensitivity analysis will be completed to examine the effectiveness of joint protection and hand exercises for those participants attending all four treatment sessions. This analysis will only be completed if there are sufficient participants attending all four treatment sessions. Treatment concordance will also be evaluated descriptively by (self-reported) frequency and duration of hand exercise completion at 3-, 6- and 12-month follow-up.

Generalisability of the trial findings and the success of the randomisation procedure will be explored descriptively by comparing key characteristics of participants at recruitment and each follow-up stage and for each randomised treatment arm. No interim analyses will be planned during the trial follow-up period.

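### The collection schedule does not support two planned analyses: exercise duration is never asked at 3 months, and three 6-month 0-10 ratings are taken only at the nurse clinic

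*Protocol article*

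**What the plan says.** **Three 0-10 ratings.** Under the heading "Self-reported questionnaire at baseline, 3, 6 and 12 months" the protocol lists a pain item, "average pain severity over the past 3 days (0-10 numerical rating scale"). The second item concerns the problem that each participant names: "severity rating of participant nominated main functional problem over the past 3 days (0-10 numerical rating scale"). The third item is a rating of how content the participant is: "satisfaction with hand function over the past 3 days (0-10 numerical rating scale"). Table 4 gives all three rows the time points 0NA, 3, 6NA, 12. That means nurse assessment at baseline and 6 months and postal questionnaire at 3 and 12 months. There is no 6Q code and no plus sign for minimum data collection. The list of clinic measures that follows in the text names grip strength, pinch strength and the grip ability test, and none of these ratings. For people who do not respond to the 6-month clinic invitation and its reminder, Recruitment and retention strategies says that "the follow-up questionnaire will be mailed to participants but without an invitation to attend the clinical assessment".

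**Exercise concordance.** The Statistical methods section will describe self-reported "frequency and duration of hand exercise completion at 3-, 6- and 12-month follow-up". In Table 5 the row "Hand exercise duration [69"] is scheduled at 6Q and 12 only, as is the times-per-week frequency row. A separate frequency item about the last week, answered from never to always, is scheduled at 0Q, 3, 6Q and 12.

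**Adverse events.** The same questionnaire list includes side effects and adverse events. Neither Table 4 nor Table 5 has a row for them. Monitoring and reporting of harms describes one route: "If a patient experiences an adverse event the OT concerned will inform the study coordinator by fax or telephone". The leaflet and advice arm has no OT classes.

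**The concern.** The protocol says that Tables 4 and 5 document the study outcomes, so whoever builds the forms is likely to work from them. Where they disagree with the text, the analysis may be promised data that no form collects, and an item not asked at the time cannot be recovered later.

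Two analyses are exposed. The 3-month description of exercise duration has no source at all, although 3 months is the follow-up closest to the four weekly classes. The three ratings are secondary outcomes, and the main analysis covers all secondary outcomes. At 6 months, the primary time point, they would be observed only in clinic attenders.

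The adverse-event mismatch is smaller. If the forms followed the tables, the one reporting route described would run through therapists whom the leaflet arm does not see.

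**Working it through.** **1. The plan's own figures.** Target sample size gives 35% versus 55%, 80% power, 5% alpha (two-sided assumed), 212 evaluable and 252 randomised.
- Without continuity correction, n per group = [1.96 × √(2 × 0.45 × 0.55) + 0.842 × √(0.35 × 0.65 + 0.55 × 0.45)]² / 0.20² = 95.9, so 96 per group and 192 in total.
- With continuity correction, n = (95.9/4) × [1 + √(1 + 4/(95.9 × 0.20))]² = 105.7, so 106 per group and 212 in total. This matches the protocol.
- 212/0.85 = 249.4, so 250. Rounded up to four equal arms this is 4 × 63 = 252.

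No stated figure is in dispute. The number used below is the expected count with 6-month data: 252 × 0.85 = 214.2, about 214.

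**2. Exercise items, text against Table 5.**

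| Item | Needed by the analysis text | Table 5 |
|---|---|---|
| Duration | 3, 6, 12 months | 6Q, 12 |
| Frequency, times per week | 3, 6, 12 months (if this is the item meant) | 6Q, 12 |
| Frequency in last week, never to always | 3, 6, 12 months (if this is the item meant) | 0Q, 3, 6Q, 12 |

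Duration at 3 months is missing for everyone, whatever is assumed. Frequency at 3 months exists only on the never-to-always scale.

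**3. Ratings, text against Table 4.** The Table 4 legend defines 6Q and 6NA separately, and neighbouring rows such as AUSCAN pain and the SF-12 use 6Q. So 6NA cannot be read as shorthand for any 6-month contact. Following the 6-month reminder route, a clinic non-responder is mailed a questionnaire that, by Table 4, does not contain these items. Someone reached only by minimum data collection also lacks them. Baseline values are safe, because everyone randomised has attended the baseline clinic.

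**4. Size of the 6-month loss.** The protocol gives no clinic non-attendance rate. As an assumption, let a share *a* of the 214.2 people with 6-month data not attend. The number without the ratings is 214.2 × *a*. The total missing share of those randomised is 0.15 + 0.85 × *a*.

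| *a* (assumed) | Lack the ratings | Have them | Missing share of 252 |
|---|---|---|---|
| 5% | 11 | 203 | 19% |
| 10% | 21 | 193 | 24% |
| 20% | 43 | 171 | 32% |

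These counts include people reached only by minimum data collection, whom a longer questionnaire would not recover.

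**5. Adverse events.** The questionnaire list covers all four arms and the tables have no row. The harms section covers therapist reports, which the 63 leaflet participants cannot generate. The text and the tables therefore imply different ascertainment, and the protocol does not say which governs.

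**The case against.** The questionnaire list is a loose summary: it also covers the medical record download, which is not a questionnaire item. The tables carry the detailed timing, and on their reading the ratings are collected at all four time points, with the same nurse mode at baseline and 6 months. That is a coherent choice for a baseline-adjusted comparison. The protocol also offers a clinic reminder, a second appointment for those who fail to attend, and multiple imputation, for which the AUSCAN subscales in the 6-month questionnaire would be informative. All of this stands, and it limits the damage. It does not give clinic non-attenders a 6-month rating, and it does not explain why the text calls the ratings questionnaire items.

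A reader might infer three stronger things that the documents do not support.
- *The ratings are lost selectively by arm.* The schedule is the same in every arm and no attendance figure is given. Differential attendance is possible, not shown.
- *Exercise after the classes cannot be described at all.* The last-week frequency item is asked at 3 months. The concordance analysis is also descriptive, so no effect estimate depends on it.
- *Harms in the leaflet arm go unrecorded.* The text places adverse events in the questionnaire for every arm. A missing table row does not show that the item is missing, because the tables are not exhaustive: the activity diary has no row either. The harms section describes what therapists do and does not call this the only route. The 6-month nurse visit also records red flags, hand injury and hand operations.

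**Conclusion.** Two contradictions in the current text hold. The 3-month exercise duration analysis cannot be produced, and this rests on no assumption. The three ratings will be missing at the primary time point for everyone who supplies 6-month data without attending the clinic: about 11 to 43 people if 5% to 20% of about 214 do not attend, a range that is assumed and not taken from the protocol. Imputation mitigates this only in part.

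The primary outcome is not touched, because AUSCAN and global change are in both the 6-month questionnaire and minimum data collection. The adverse-event mismatch is minor: it is a matter of reconciling text and tables, not evidence that harms go uncollected.

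**What to change.** 1. Add the duration and times-per-week items to the 3-month questionnaire and correct Table 5. If that form can no longer change, limit the 3-month description in Statistical methods to the last-week frequency item.
2. Put the three ratings in the 6-month questionnaire, at least in the copy mailed to clinic non-attenders, and correct Table 4 to match the text. State which value is analysed if a person has both, and report the number obtained by each mode in each arm.
3. Reconcile the questionnaire list, Tables 4 and 5 and the harms section on adverse events. Base any between-arm harms comparison on the all-arm questionnaire item, not on therapist reports.

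The cost is five short items and a minor amendment: a small added burden for respondents, and some mixing of nurse and postal mode in the 6-month ratings. The change recovers people who return the mailed form, but not those reached only by minimum data collection.
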